### Objectives {7}

#### Research hypotheses

There is a volume dose-response effect of HIFT on blood lipids, glucose metabolism, endothelial function, fitness, and body composition.

There is an inverse dose-response effect of HIFT on the perception of “exercise enjoyment” and “intention to continue.”

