### Trial design {8}

The present study is a parallel-group, three-arm, exploratory, randomized, dose-response clinical trial. Randomization is at a 1:1:1 allocation ratio for the three arms.

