#### Tertiary outcomes

##### Exercise questionnaires

To assess the participant’s level of “enjoyment” and “intention to continue” their allocated HIFT intervention, a questionnaire will be administered post-training. For enjoyment assessment, the Physical Activity Enjoyment Scale (PACES) will be used [91]. The PACES is an 18-item, 7-point, bipolar rating scale. For the intention to continue assessment, two additional items will be added regarding (1) how likely the participant would continue performing that modality (0 = very unlikely, 10 = very likely) and (2) how many days per week the participant would consider performing that modality (0–7 days) [92, 93]. Data will be aggregated as mean ± SD for each dose group and subgroups. The mean ± SD will be compared between the 3 dose groups and subgroups.

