#### Sample size {14}

The sample size was projected with a change in ApoB as the main outcome variable between HIFT1 and HIFT3. Power calculations (IBM SPSS v25 Armond, NY) assumed a 1:1 equal allocation between HIFT1 and HIFT3. The baseline mean and standard deviations from a previous study [97] and pilot studies for ApoB were ~ 129 ± 25 mg/dL in sedentary adults with elevated cardiometabolic risk. Collectively, using these data, we consider a 15% reduction in ApoB to be clinically meaningful within the HIFT3 group [98]. Assuming a power of 0.90, *α* = 0.05, and an effect size of *d* = 0.80, a paired samples one-tailed *t*-test sample size calculation revealed a sample size of 60 subjects (20 per group) will establish the superiority of HIFT3 versus HIFT1 for pre- to post-differences in the primary outcome ApoB. With an estimated 5% dropout rate, we will recruit 22 subjects/group to obtain the necessary sample size of 60. Therefore, a total of 60 men and women who meet the previously stated inclusion criteria will be recruited and randomized post-baseline assessments into one of the three intervention groups. Data will be collected in cohorts of 12, randomized into intervention groups. This will continue until 20 participants per intervention group have completed the study. This will accommodate dropout within cohorts.

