## Statistical methods

### Statistical methods for primary and secondary outcomes {20a}

Only data from participants who complete ≥ 80% of total exercise intervention and with no noticeable change in eating (statistically different energy consumption and macronutrient distribution) and physical activity habits will be included [97, 99, 100]. All data will be analyzed using the Statistical Package for the Social Sciences (IBM SPSS v25, Armond, NY). Descriptive data if normal will be presented as mean ± SD, or median and interquartile range if not normal; the significance level of all comparative data will be set as *p* ≤ .05, and normality will be assessed using a Kolmogorov-Smirnov test. If normality exists, parametric tests will be used, if normality does not exist, non-parametric tests will be used. Effect sizes (ES) and confidence intervals (CI) will be calculated on the results of all dependent variables. Paired *t*-tests will be used to evaluate the significant differences between pre- and post-measures of both primary and secondary physiological outcomes within each group. A one-way ANOVA will be used to compare the primary and secondary outcomes pre-post mean change between the three groups. When indicated by a significant *F* value, post hoc analysis will be determined using the Bonferroni adjustment for multiple comparisons. The median, mode, and interquartile ranges of the IFIS and PACES data will be calculated for each of the three groups. Should missing data in outcomes occur, a linear-mixed model will be conducted instead of ANOVA as this test accounts for missing data.

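### The HIFT3 versus HIFT1 comparison of ApoB change that sized the trial is tested only after a significant ANOVA F and with a Bonferroni penalty, which cuts its power from about 70% to about 53%

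*Protocol article*

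**What the plan says.** **Hypotheses.** The Research hypotheses section states two ordered claims. For the physiological outcomes: "There is a volume dose-response effect of HIFT on blood lipids, glucose metabolism, endothelial function, fitness, and body composition". For enjoyment and intention to continue: "There is an inverse dose-response effect of HIFT on the perception of", followed by those two constructs.

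**Design and size.** Under Trial design {8}: "Randomization is at a 1:1:1 allocation ratio for the three arms". Sample size {14} takes change in ApoB, HIFT3 against HIFT1, as the comparison to be powered: "Assuming a power of 0.90, *α* = 0.05, and an effect size of *d* = 0.80". It names a one-tailed paired t-test and arrives at 20 per group. It also calls a 15% ApoB reduction within HIFT3 clinically meaningful and gives a baseline of about 129 ± 25 mg/dL.

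**Analysis.** Section {20a} plans paired t-tests within each arm, then a one-way ANOVA of pre-post change for primary and secondary outcomes. Pairs follow only a significant F, and "post hoc analysis will be determined using the Bonferroni adjustment for multiple comparisons". The threshold is general: "the significance level of all comparative data will be set as *p* ≤ .05", with no side stated. Effect sizes and confidence intervals are promised for all dependent variables. A linear mixed model replaces the ANOVA if outcome data are missing. Sections {20a}, {20b} and {20c} contain no trend test, dose contrast or numeric dose term.

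**Enjoyment.** For the Physical Activity Enjoyment Scale (PACES), section {20a} says: "The median, mode, and interquartile ranges of the IFIS and PACES data will be calculated for each of the three groups". The Exercise questionnaires paragraph under Outcomes {12} says of PACES and the intention items: "The mean ± SD will be compared between the 3 dose groups and subgroups".

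**The concern.** The trial was sized on one pre-declared contrast, but the analysis gives that contrast no standing of its own. It is reached only through a two-degree-of-freedom test that ignores the order of the arms, and then shares its error rate with the two comparisons involving HIFT2. A true HIFT3 advantage of the size the trial was designed around could go unreported because F fell short or because the pair missed 0.0167. The sample size section presents the trial as able to establish superiority of HIFT3 over HIFT1, and the planned test does not match that claim.

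A smaller matter is that the two accounts of the enjoyment data use different summaries, and only one of them speaks of comparing arms.

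**Working it through.** **Inputs.** From Sample size {14}: 20 per arm, d = 0.80, power 0.90, α = 0.05, baseline 129 ± 25 mg/dL, 15% reduction. From {20a}: one-way ANOVA, then Bonferroni pairs at p ≤ .05. Assumed: d is the HIFT3 minus HIFT1 difference in mean change divided by the SD of change; tests are two-sided; Bonferroni covers the three pairs (α/3 = 0.0167).

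**Step 1. The plan's own figure.** A one-tailed paired t-test at d = 0.80 and 90% power needs 15, not 20; the two-tailed version needs 19. Neither is a between-arm test. A two-sample comparison at d = 0.80 needs 28 per arm one-sided or 34 two-sided. That mismatch is a separate matter. Here, 20 per arm and d = 0.80 are taken as given.

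**Step 2. The contrast without gate or adjustment.** With weights (−1, 0, 1) and pooled error, df = 3 × 19 = 57. Noncentrality = 0.80 / √(2/20) = 2.53. The two-sided 5% critical value is 2.00. Power = 0.70 (0.80 if one-sided at 5%).

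**Step 3. The planned route.** Take equally spaced true means of 0, 0.4 and 0.8 SD.
- Omnibus F: λ = 20 × (0.4² + 0² + 0.4²) = 6.4 on (2, 57) df; power = 0.59.
- HIFT3 versus HIFT1 at α/3: critical value 2.47, same noncentrality 2.53; power = 0.53.
- Both significant, by simulation: 0.52 to 0.53.

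The gate removes little beyond the adjustment, so most of the loss comes from α/3. Simulated power for F followed by an unadjusted pair is about 0.57.

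**Step 4. Other response shapes**, 20 per arm:

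| True means (SD) | F | Two-sided contrast | F, then Bonferroni pair |
|---|---|---|---|
| 0 / 0.4 / 0.8 | 0.59 | 0.70 | 0.53 |
| 0 / 0.6 / 0.8 | 0.63 | 0.70 | 0.53 |
| 0 / 0 / 0.8 or 0 / 0.8 / 0.8 | 0.72 | 0.70 | 0.53 |
| 0 / 0.8 / 0.4 | 0.59 | 0.24 | not computed |

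**Step 5. Sensitivity to the SD of change.** The article gives only the baseline SD. With SD of change = 25 × √(2(1 − r)) and a difference of 0.15 × 129 = 19.35 mg/dL, linear pattern:

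| r (assumed) | SD of change | d | F | Contrast | F, then Bonferroni pair | Gain in points |
|---|---|---|---|---|---|---|
| 0.5 | 25.0 | 0.774 | 0.56 | 0.67 | 0.49 | about 18 |
| 0.8 | 15.8 | 1.22 | 0.93 | 0.97 | 0.91 | about 5 |

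**Step 6. Sample size equivalent.** For 90% power at d = 0.80, linear pattern, the arm size needed is 34 for the two-sided contrast, 41 for F and 44 for the Bonferroni pair.

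**The case against.** **An omnibus F is a legitimate choice in a trial that calls itself exploratory.** This stands in part. The ANOVA controls error and makes no assumption about shape, and the Discussion cites a dose study in which the lowest dose matched higher ones on visceral fat. For a non-monotone response such as 0/0.8/0.4 SD the linear contrast does much worse (0.24 against 0.59). That is a reason to keep the ANOVA as a secondary analysis. It does not justify making the sized comparison depend on it.

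**The contrast tests dose-response no better.** A reader might infer that the trial as planned cannot state a dose gradient and that a linear contrast would cure this. It would not. With three equal, equally spaced arms, HIFT2 has zero weight, so a significant contrast cannot separate a gradient from a step or plateau. The gain over the planned pair comes from removing the gate and the adjustment from the comparison the trial was sized on.

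**Bonferroni after F is invalid.** A reader might infer this too. It is conservative, not wrong: with three arms a significant F already protects unadjusted pairs. Dropping only the adjustment adds about 5 points under the linear pattern (0.57 against 0.52).

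**Enjoyment has no test at all.** This goes too far. The Outcomes section commits to a between-arm comparison, {20a} concerns primary and secondary outcomes while enjoyment is tertiary, and the exact test may be left to an analysis plan that is not shown. What remains is the mismatch in summaries.

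**The minimal dose will be declared from within-arm p-values.** The article does not say so. It also promises effect sizes and confidence intervals, and it states the 15% figure only for HIFT3.

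**Conclusion.** The concern holds for the primary between-arm test. The contrast on which the trial was sized has about 53% power under the planned analysis and 70% if pre-specified, at 20 per arm and d = 0.80 read as a between-arm difference in SDs of change. The 53% does not depend on where HIFT2 lies between the other two arms. The size of the loss does depend on the SD of change: about 18 points at a pre-post correlation of 0.5 and about 5 at 0.8, for a 15% difference. Under a single step, F itself is about 2 points above the contrast (0.72 against 0.70), but the sized pair remains at 0.53.

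This is a mismatch between sizing and testing that should be corrected. It does not make the analysis invalid. Pre-specifying the contrast does not reach the stated 90% at d = 0.80 with 20 per arm, and the article supports no wider claim about enjoyment or the minimal dose than the limited ones above.

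**What to change.** In {20a}:

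1. Name as the primary between-arm test the two-sided one-degree-of-freedom linear dose contrast for ApoB change. With three equal arms this is HIFT3 minus HIFT1 with the pooled error. Test it at 0.05, report its 95% CI, and do not make it conditional on F. State that the same contrast is taken from the linear mixed model if that replaces the ANOVA.
2. Keep the ANOVA and the pairwise comparisons as secondary analyses, to describe the shape of the response and the place of HIFT2 and to cover non-monotone patterns.
3. Report each arm's mean ApoB change and CI alongside the 15% figure, and label the within-arm paired p-values descriptive.
4. Reconcile the Outcomes section with {20a} for PACES and the intention items: choose one summary, and compare arms with the same dose contrast or an ordered non-parametric test such as Jonckheere-Terpstra.

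The cost is analysis wording, with no new data or participants. The price is about 2 points of power against F if the response is a single step, and considerably more for the primary test if the response is non-monotone, which is why item 2 stays.

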### Interim analyses {21b}

Due to the nature and length of the intervention, no interim analyses will be performed.

### Methods for additional analyses {20b}

To explore whether the outcomes vary significantly between men and women, a secondary analysis will be performed for the stratification variable of sex.

### Methods in analysis to handle protocol non-adherence and any statistical methods to handle missing data {20c}

Participant adherence will be determined by completion of ≥ 80% of total exercise intervention and no noticeable change in eating and physical activity habits, assessed by the Block questionnaires. Should non-adherence occur, outcome variables will be tested using two analysis sets: the intention-to-treat set, considering all randomized participant data regardless of intervention adherence, and the per-protocol set, considering only data from participants who complete ≥ 80% of the total exercise intervention. Analyses will be performed to examine the effect of the different strategies on the conclusions. If intention-to-treat analyses are determined appropriate, reasons for withdrawal will be reported and compared qualitatively. If missing outcome variables occur, imputation of missing data will be considered. To account for missing data, a linear mixed-model analysis will be used to determine if there are differences in the primary outcome variable of ApoB.

### Plans to give access to the full protocol, participant-level data, and statistical code {31c}

This document is the full protocol. Anyone interested in other data or documentation should contact the corresponding author.

### Oversight and monitoring

#### Composition of the coordinating center and trial steering committee {5d}

The trial will be overseen by a trial steering committee (TSM) consisting of the principal investigator, [name], and the advising investigators, [name], [name], and [name]. This TSM will meet every 5–6 weeks via a mix of teleconference and personal meetings. The group will discuss the current trial status as well as any decision-making for the upcoming 5–6 weeks.

#### Composition of the data monitoring committee, its role, and reporting structure {21a}

Due to the low risk, complexity, and scope of the intervention, data and safety monitoring will be performed throughout the entire trial by the TSM. However, a data and safety monitoring board (DSMB), consisting of external members with clinical and methodological expertise, will become involved if an unlikely adverse event occurs. In this case, the board will receive a report of the event and advise the TSM on the continuation and modification of the trial.

#### Adverse event and reporting and harms {22}

An adverse event is defined as a medical condition occurring between the time of consent and the last trial visit that results in the inability to participate in the intervention. A serious adverse event is defined as any untoward medical occurrence that results in an immediately life-threatening condition, severe or permanent disability, prolonged hospitalization, or significant hazard as determined by the DSMB. Any adverse event or serious adverse event between the time of participant consent and the last trial visit will be recorded on the WCU HAP Lab Incident Report Form at the time of the event. If the adverse event occurs after the time of consent but before receiving the intervention, the event will be recorded as not related to the study. If the event occurs between the first and last intervention visit, the event will be reported to the DSMB. In the case of a serious adverse event, the event will be reported to the Institutional Review Board (IRB) at Western Colorado University and Ethics Committee at Auckland University of Technology. Investigators and DSMB will determine the relatedness of an event to the study intervention. Adverse events deemed related to the study will be reported in the results of the study.

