#### Criteria for discontinuing or modifying allocated intervention {11b}

Participants may choose to stop the HIFT intervention for any reason. There are no special criteria for modifying the allocated intervention. Modification of the exercises within the intervention will be determined on an individual basis if a participant cannot perform the exercise properly. An alternative exercise will be chosen that targets the same muscle group and performed at the same target intensity.

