#### Participant timeline {13}

Upon recruitment, participants will meet with the primary investigator and provide informed consent and health history. Next participants will be screened for the inclusion criteria at the HAP Lab at WCU. During the screening visit, participants’ height, weight, waist circumference, abdominal height, resting HR, resting BP, and resting SpO_2_ will be measured. Additionally, participants will be measured for a fasted basic blood lipid and glucose panel. Next, participants will complete a physical activity and diet questionnaire (Full Block Questionnaire, NutritionQuest, 2014) [70, 71], and all included participants will be asked to maintain their self-reported diet throughout the entire study.

Participants will begin the study with a baseline GXT immediately after the initial screening. Next, baseline metabolic testing in the HAP Lab and GVH will take place 48–72 h after. This visit will consist of a 12-h overnight fast, baseline endothelial function testing at the HAP Lab, then metabolic marker bloodwork and body composition testing via DEXA at GVH. Additionally, participants will complete the IFIS to assess self-reported fitness [85, 86]. During the following 3 weeks, participants will visit the HAP Lab twice a week for exercise familiarization and adaptation. Participants will then be randomized into 1 of 3 exercise dose groups (HIFT1, 1 session per week; HIFT2, 2 sessions per week; HIFT3, 3 sessions per week) and be scheduled for their exercise sessions for the following 12 weeks. The 12 weeks of supervised training will consist of three 4-week phases, where intensity and duration of exercise are progressed each phase. After the last exercise session, participants will be scheduled for two post-testing visits. The first visit will consist of a 12-h overnight fast, endothelial function testing, PACES and exercise intention questionnaires, and IFIS questionnaire at the HAP Lab, then metabolic marker bloodwork and body composition testing via DEXA at GVH. This visit will be scheduled no sooner than 48–72 h after the final exercise session to ensure acute lipid or glucose responses are not influenced [14, 94–96]. The second visit, 24–48 h later, will consist of the repeated GXT on a treadmill from baseline testing. See Fig. 2 for the schematic illustration of research design and Table 3 for the schedule of the study period.

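### Events that do not stop participation need not be recorded, and neither death nor a new admission is named as serious, so the harm record may be incomplete

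*Protocol article*

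**What the plan says.** All the harms definitions are in the protocol article, Adverse event and reporting and harms {22}.

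- **Adverse event:** a medical condition "that results in the inability to participate in the intervention".
- **Serious adverse event:** an untoward occurrence resulting in an "immediately life-threatening condition, severe or permanent disability, prolonged hospitalization, or significant hazard as determined by the DSMB". These four criteria do not depend on whether participation stops.
- **Recording:** "Any adverse event or serious adverse event between the time of participant consent and the last trial visit will be recorded" on the laboratory's incident form.
- **Relatedness:** for an event after consent but "before receiving the intervention, the event will be recorded as not related to the study".
- **Routing:** events between the first and last intervention visits go to the DSMB. Serious events go to the IRB and the ethics committee.
- **Results:** "Adverse events deemed related to the study will be reported in the results of the study".

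The sections on the data monitoring committee {21a} and on auditing {23} bring in the DSMB when an adverse event occurs. They give no definition of their own. Section {31c} says that the article is the full protocol.

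**The concern.** A harms definition should capture an untoward event first and judge its importance and cause afterwards. Here the effect on attendance decides whether a non-serious event exists for the trial at all. The serious list leaves out death and mentions hospital care only when it is prolonged. Relatedness then decides what the results are committed to show.

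The trial compares three weekly frequencies of high-intensity training in sedentary adults with metabolic syndrome, and its Discussion expects the findings to feed into exercise programming guidelines. Readers choosing between frequencies will want to see what harm occurred at each. If minor and moderate events are never written down, no later analysis can recover them.

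**Working it through.** The protocol states no harms rate or safety figure, so there is nothing to reproduce. The check applies the rules in section {22} to kinds of event that could occur.

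**Exposure.** Twelve weeks at 1, 2 or 3 sessions per week gives 12 × 1 = 12, 12 × 2 = 24 and 12 × 3 = 36 planned sessions. The highest arm has 36 / 12 = 3 times the training exposure of the lowest.

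**Applying the definitions.**

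| Event | Adverse event? | Serious? | Recording required? |
|---|---|---|---|
| Non-serious injury or symptom in the training weeks, participation continues | No | No | No |
| Non-serious event at the post-training exercise test | No, training is over | No | No |
| Short admission, participation continues | No | Only through another criterion, such as the hazard judged by the DSMB | Only if serious |
| Short admission that stops training | Yes | As in the row above | Yes |
| Death during the training weeks | Yes, it ends participation | By interpretation, through the life-threat or hazard criterion | Yes |

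**The post-training test.** Participant timeline {13} places two testing visits after the last exercise session. The second repeats the graded exercise test. The Graded exercise test section takes that test to volitional exhaustion and follows it with a verification bout at 105% of maximal workload. The recording window in {22} stays open until the last trial visit, so the test lies inside it. Nobody can be made unable to take part in an intervention that has finished, so a non-serious event at this test cannot meet the definition. The window and the definition do not fit together.

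**The baseline test.** The same timeline says "Participants will begin the study with a baseline GXT immediately after the initial screening". An event there that prevents participation is recorded but classed as unrelated by rule, although the study's own maximal test may have caused it. It then falls outside the commitment on results. It precedes randomization, so it bears on the overall harm record and not on the comparison of arms. The protocol does not say whether the three familiarization weeks count as receiving the intervention.

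**Routing.** IRB and ethics committee reporting is stated for serious events. DSMB involvement is triggered by an adverse event. Both therefore inherit the definitions above.

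**The case against.** The strongest reply is that grave events are not lost. A death or a training-stopping admission during the programme is an adverse event and goes on the incident form. If it falls between the first and last intervention visits, it also goes to the DSMB, which then advises on continuation. This stands. What remains is that its classification as serious, and with it the stated route to the IRB and ethics committee, rests on interpretation or DSMB judgement and not on a listed criterion.

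Second, the sentences on reporting do not contain the word only, and section {20c} provides, conditionally, for reasons for withdrawal to be reported. This is partly right: nothing forbids fuller reporting. But the stated commitment covers related events alone, and withdrawal reasons cannot reveal events that did not lead to withdrawal.

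Third, inability to participate could be read as missing a single session. That would capture more events. It would also make the recording of a short-lived condition depend on how often the participant is scheduled, which is what differs between arms.

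Fourth, an article may leave detail to a fuller document. That does not help here: the definitions are stated outright, and the article says that it is the full protocol.

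Some stronger readings are tempting but are not supported:

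- **Exercise substitution hides injuries.** Section {11b} says "Modification of the exercises within the intervention will be determined on an individual basis if a participant cannot perform the exercise properly". It speaks of improper performance and does not mention injury.
- **IRB review of short admissions is delayed.** No reporting timeline is given, so no delay can be shown. At most, such an admission might not be routed there.
- **Harm by dose is half of what the trial sets out to answer.** The stated aims concern cardiometabolic markers, fitness, body composition, enjoyment and intention to continue. No safety aim is stated.
- **More injuries will be missed in the higher-frequency arms.** The threefold difference is one of exposure. It gives no injury count and no rate of under-recording.

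**Conclusion.** The point holds as a defect in the wording of section {22}, and it should be corrected. Followed as written, non-serious events that do not stop participation need not be recorded, non-serious events at the post-training maximal test cannot qualify, and a short admission is serious only through some other criterion. The record of harm across the three arms may therefore be incomplete.

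The size cannot be estimated: the protocol gives no event rate, and the session counts establish exposure only. The conclusion assumes that staff apply the definitions literally and that no wider definition exists elsewhere. None was found in the article. A reader might infer that deaths would go unrecorded. The text does not support that; only their classification as serious is left open.

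**What to change.** In section {22}:

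1. Define an adverse event as any untoward medical occurrence from consent to the last trial visit, whether or not it stops participation. This also brings the post-training test under the definition.
2. Add death and any inpatient admission, new or prolonged, to the serious criteria, keeping those already listed.
3. Report all adverse events by arm, with relatedness shown as a descriptor and not used as a filter. Events before randomization can be listed separately.

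The cost is a text amendment and slightly more recording by session and testing staff on the existing incident form. Because the DSMB is triggered by an adverse event, the wider definition would also send it more minor events, so the amendment should say which events require its involvement.

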#### Intervention description {11a}

For 3 weeks prior to the 12 weeks of training, participants will undergo exercise familiarization 2 days/week. Participants will then be randomized into 1 of 3 exercise dose groups (HIFT1, 1 session per week; HIFT2, 2 sessions per week; HIFT3, 3 sessions per week). Then, 12 weeks of supervised training will commence consisting of three 4-week phases, where intensity, duration of exercise, and recovery time are progressed each phase.

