##### Three-week adaptive period

Twice a week for 3 weeks, participants will visit the HAP Lab to learn proper techniques and familiarize themselves with HIFT exercises. Week 1 will consist of a movement screening to assess the participant’s capabilities of multi-planar, functional movements (squat, hinge, lunge, push, pull, press, and rotation) [74, 75]. Corrections and modifications will be advised to participants, then movements will be trained to ensure proper, safe exercise. If proper movement is not attained within week 1, this familiarization will be extended until satisfaction before progression. Week 2 will consist of learning a structured HIFT routine using minimal load at half of phase 1 volume (see Fig. 1). Week 3 will consist of HIFT rehearsal bouts at ¾ of phase 1 volume (see Fig. 1). Load or resistance will be added to the exercise on an individual basis, aiming for a target perceived effort of ≥ 7 on the Borg Session RPE CR10 Scale (sRPE) [76–79]. Examples of load or resistance are bodyweight, suspension bands, medicine balls, kettlebells, dumbbells, elastic bands, and stability balls. Additionally, participants will be familiarized with the aerobic intensity target (HR ± 5 beats of second ventilatory threshold (VT2)) for each set within the HIFT session. To quantify these intensity targets, HR and sRPE will be measured immediately after each set. Participants will be familiarized with this data collection procedure and intensity target during week 3 [79]. Participants will then be randomized and scheduled for their 12 weeks of training based on their allocated dose (HIFT1, HIFT2, or HIFT3).

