#### Relevant concomitant care permitted or prohibited during the trial {11d}

To isolate the effects of the intervention alone, all participants will complete a physical activity and diet questionnaire [70, 71] prior to the start of the study. Participants will be asked to maintain the same behaviors throughout the study, then fill out the questionnaires midway and after the study to verify. Participants will be informed that any additional dietary and exercise interventions will be prohibited throughout the study.

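### Adverse events are defined by inability to take part and recorded on an event-time form, while scheduled participation is the randomised factor, so any description of harms by dose risks unequal ascertainment of short conditions

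*Protocol article*

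**What the plan says.** The section on adverse events and harms ({22}) sets the scope widely: "Any adverse event or serious adverse event between the time of participant consent and the last trial visit" is to be recorded. The only instrument it names is the laboratory's incident form, on which events "will be recorded on the WCU HAP Lab Incident Report Form at the time of the event". It describes no adverse-event question put to all arms at fixed times. An adverse event is a medical condition "that results in the inability to participate in the intervention". Events judged related to the study will appear in the results.

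The intervention description ({11a}) sets the arms as "HIFT1, 1 session per week; HIFT2, 2 sessions per week; HIFT3, 3 sessions per week", and "12 weeks of supervised training will commence consisting of three 4-week phases". Under Trial design ({8}), "Randomization is at a 1:1:1 allocation ratio for the three arms".

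The section on concomitant care ({11d}) gives every arm the same diet and physical-activity questionnaires before the study; participants "then fill out the questionnaires midway and after the study to verify". No adverse-event item is mentioned there.

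**The concern.** Two features of the harms plan are tied to the randomised factor.

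- **Definition.** Whether a condition prevents participation depends on whether a session was due while it lasted. A brief complaint that starts and ends between two weekly sessions need not stop a HIFT1 participant from doing anything, so it may not qualify as an adverse event. The same complaint in a HIFT3 participant is likely to fall on a session day, and then it qualifies. Perfect reporting would not remove this difference.
- **Recording route.** The form is completed at the time of the event. During training, the regular occasions on which staff see participants are the supervised sessions, and their number differs by arm.

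The trial is meant to inform clinicians about the minimum useful weekly dose, and dose is the only planned difference between the arms. Readers are likely to look at published events by dose even without a formal test. Identical true rates of short conditions could then look like fewer events at the lowest dose. Oversight is also touched: by the sections on data monitoring ({21a}) and auditing ({23}), the external board becomes involved when an adverse event occurs, and a complaint that does not count as one does not bring it in.

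**Working it through.** The article gives no adverse-event rate, duration or detection figure, so there is no stated number to reproduce. The check has two parts.

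**1. Scheduled contacts by arm**

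Inputs: 1, 2 or 3 sessions per week for 12 weeks ({11a}); two post-testing visits and two visits before familiarisation, namely screening with the first exercise test and baseline testing ({13}); six familiarisation visits, since "Twice a week for 3 weeks, participants will visit the HAP Lab" gives 2 × 3 = 6.

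| Count | HIFT1 | HIFT2 | HIFT3 | HIFT3 : HIFT1 |
|---|---|---|---|---|
| Training sessions (12 × sessions per week) | 12 | 24 | 36 | 36/12 = 3.0 |
| After randomisation (+ 2 post-testing) | 14 | 26 | 38 | 38/14 = 2.7 |
| Whole study (+ 2 + 6 before randomisation) | 22 | 34 | 46 | 46/22 = 2.1 |

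**2. Chance that a condition of D days meets a scheduled session**

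Assumptions, none of them from the article:

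- onset is uniform over the week;
- a condition counts only if a session falls while it lasts, with no later report;
- HIFT1 trains on one fixed day, HIFT2 on Monday and Wednesday, HIFT3 on Monday, Wednesday and Friday. (The article schedules sessions on those three days but lets participants attend according to their own schedules and dose group.)

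For a weekly schedule with gaps g between sessions, the share is the sum of min(D, g) over the gaps, divided by 7. The gaps are 7 days in HIFT1; 2 and 5 in HIFT2; 2, 2 and 3 in HIFT3.

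| D (days) | HIFT1 | HIFT2 | HIFT3 | HIFT3 / HIFT1 |
|---|---|---|---|---|
| 1 | 1/7 = 14% | 2/7 = 29% | 3/7 = 43% | 3.0 |
| 2 | 2/7 = 29% | 4/7 = 57% | 6/7 = 86% | 3.0 |
| 3 | 3/7 = 43% | 5/7 = 71% | 7/7 = 100% | 2.3 |
| 5 | 5/7 = 71% | 7/7 = 100% | 7/7 = 100% | 1.4 |
| 7 or more | 100% | 100% | 100% | 1.0 |

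The threefold ratio holds for conditions of up to about 2 days, shrinks after that and disappears at one week.

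**The case against.** A reader might infer that adverse events are captured only when staff see them, that HIFT3 is therefore observed three times as often as HIFT1, and that harms by dose are biased. The document does not support that.

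- **Scope.** The section requires any event from consent to the last visit to be recorded. The form is where events are written down; the text does not say how they come to light. A participant can report a problem by message or at the next visit.
- **No planned comparison.** No aim, hypothesis or analysis section compares harms between doses. The article says only that related events will be reported.
- **Ratio.** Three to one is right for training sessions alone; it is 2.7 after randomisation and 2.1 over the whole study.
- **Model.** Uniform onset suits illness between sessions, not injuries during exercise, which happen under supervision in every arm. Participants may also have some freedom to choose their day, so a short HIFT1 problem need not cost a session.
- **Exposure.** Extra harm caused by more sessions is part of the effect of dose, not a bias.

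All of these stand, and they limit the point to a risk. They do not remove it. The wide scope applies to adverse events as defined, and the definition depends on scheduled participation, so a short complaint in HIFT1 may never fall within that scope. Nor is this a detail left to a document not shown: the definition and the recording route are both stated, and the article describes itself as the full protocol ({31c}).

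**Conclusion.** The concern holds in a limited form. Because an adverse event is defined by inability to take part, the only recording route named is an event-time form, and scheduled participation is randomised, any description of harms by dose risks unequal ascertainment of conditions shorter than about a week. The 2-day and 3-day ratios of 3.0 and 2.3 show the mechanism under assumed uniform onset, assumed weekdays and no later reporting. They are not estimates of bias, because the article gives no event rates or durations. Conditions lasting 7 days or more meet a session in every arm. No planned efficacy analysis is affected and no planned harms comparison is invalidated. This is an inexpensive improvement to safety data that would sit beside a minimal-dose conclusion.

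**What to change.** Add one adverse-event item, identical in all arms, to the existing midway and post-study questionnaires. Word it without reference to missed sessions, so that it does not inherit the dose-dependent definition. The midway item should cover the time since training began, and the post-study item the time since midway. Base any description of harms by arm on these answers. Report incident-form events separately, per participant and per session attended, so that the effect of exposure can be seen.

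The cost is one item at two existing contacts and one extra table. The downside is some recall error over about 6 weeks per window (taking midway as about training week 6, which the article does not define). Participants know their allocation, so equal recall across arms cannot be guaranteed, but the schedule of asking would be the same.
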